### Study Setting

We will conduct this study in 4 subcounty HIV Comprehensive Care Clinics (CCC) in Homa Bay County, Kenya—Mbita, Ogongo, Ndhiwa, and Pala. Homa Bay County was chosen for its highest HIV prevalence, 16.2% [18] in Kenya, making it suitable to assess the implementation process and outcomes of an mHealth intervention for enhancing HIV care. The county covers an area of about 3154 km^2^ [38,39]. As of the 2019 Kenya National Census, it had an estimated population of approximately 1.1 million people [39]. There are approximately 160 health facilities providing HIV comprehensive care services across the county. ART uptake is at 96%, while viral load suppression (VLS) prevalence is at 83.8% among people living with HIV, with significant disparities between men and women [18,27,40].

The 4 health facilities have been selected based on feasibility factors such as patient volume and mobile network coverage, representativeness of diverse service delivery contexts, and requirements of the stepped-wedge design to ensure adequate clusters while minimizing contamination. They serve a total of 1899 men living with HIV aged 18‐55 years: Mbita (n=758), Ogongo (n=294), Ndhiwa (n=598), and Pala (n=249). The average distance between each neighboring facility is 25 km. Mbita and Ndhiwa subcounty hospitals are situated in an urban setup, while Ogongo and Pala subcounty health centers are located in relatively rural setups.

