#### Outcomes

The primary clinical outcome will be missed clinic appointments, while secondary outcomes will include ART adherence (30-day percent visual analog), pharmacy refill consistency (medication possession ratio), and VLS—plasma HIV RNA <200 copies per milliliter. CCC data will be retrieved from facility electronic medical records and patient files, focusing on routinely collected HIV care indicators.

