#### Stepped-Wedge Analysis

We will analyze intervention effects using intention-to-treat principles and generalized linear mixed models appropriate to each outcome. Models will include a fixed effect for time period (step) to account for secular trends, a fixed indicator for intervention exposure during each step (within-cluster), and random intercepts for clusters (facilities) to account for within-cluster correlation. Where appropriate, we will include random slopes for time if supported by the data. Covariates prespecified for adjustment include patient-level baseline characteristics (age, gender, income, education, and stigma) and facility-level covariates (facility size and urban or rural). We will use robust SEs (cluster-robust SEs) to ensure valid inference with a limited number of clusters. Additional sensitivity analyses will include per-protocol analyses and models testing for time-by-intervention interaction to explore whether effect sizes change across steps. Primary inference will be 2-sided with *α*=.05. Analyses will be performed in Stata (StataCorp LLC; xtmelogit/xtmixed), and code will be archived with the study repository for reproducibility.

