#### Power Estimation for Stepped Wedge Analysis

Sample size and power were estimated for the stepped-wedge cluster design using simulation under a Hussey-Hughes mixed effects logistic model. With facility totals of 1899—Mbita (n=758), Ogongo (n=294), Ndhiwa (n=598), and Pala (n=249), assuming baseline missed-appointment proportion (p0) of 20% (0.20) and 5 periods, the study has ~80% power to detect an intervention effect (missed visits) corresponding to an odds ratio of 0.75, assuming intracluster correlation coefficient=0.02 (*α*=.05). Sensitivity analyses indicated that power remained ≥70% for odds ratios of 0.80 and intracluster correlation coefficient values up to 0.05 and exceeded 90% for odds ratios of ≤0.70, supporting the robustness of the proposed sample size.

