#### Quantitative Data Collection and Storage

Quantitative data will be collected at baseline, at 8-month follow-up, and via the Nishauri app data. At baseline, potential participants will be screened for eligibility. Eligible participants will provide written informed consent and locator information before undergoing a short baseline survey lasting approximately 40 minutes. The survey includes validated and pilot-tested modules on sociodemographics, technology acceptance, HIV-related stigma, health literacy, masculinity norms, the System Usability Scale, and intervention acceptability. The survey will be administered electronically using tablets with the REDCap (Research Electronic Data Capture) platform, hosted by the San Francisco Coordinating Center. Data will be collected by trained research assistants (RAs), who were locally recruited and had prior experience in health or social science research. RAs have backgrounds in public health or related disciplines; are fluent in English, Kiswahili, and Dholuo; and will receive study-specific training on the study protocol, ethical conduct of research, informed consent, and standardized data collection procedures prior to data collection. RAs will perform daily quality checks on all forms to identify and resolve errors prior to secure upload to REDCap servers. These servers are firewall-protected, regularly backed up, and housed in a secure environment.

Throughout implementation at each site, app-based metrics will be assessed to capture implementation outcomes related to acceptability and uptake of the Nishauri intervention. Facility-based data will be collected, including who gets the intervention, the date of training, and the date of app installation. App analytics will be used to capture patterns of engagement and uptake among participants. This includes the number of log-ins per user, frequency of use over time, cumulative duration of app sessions, and responsiveness to reminders and notifications (whether SMS or in-app prompts were opened or acted upon). Aggregate metrics such as average log-ins per month, median engagement time, and drop-off points will be analyzed to assess acceptability and sustained use across the study period.

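### The prespecified stepped-wedge covariates include stigma, described only for the survey subset, and gender, which is constant, so the adjusted model cannot be fitted as listed to the 1899 men the study was powered on

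*Protocol article*

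**What the plan says.** Under Stepped-Wedge Analysis the article describes generalized linear mixed models on intention-to-treat principles, with fixed period effects, an exposure indicator and random facility intercepts. A separate sentence then lists the adjustment set: "Covariates prespecified for adjustment include patient-level baseline characteristics (age, gender, income, education, and stigma) and facility-level covariates (facility size and urban or rural".

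The population is defined elsewhere. Study Setting says of the facilities: "They serve a total of 1899 men living with HIV aged" 18 to 55 years. The power section uses the same count: "With facility totals of 1899". The Strategy section says the individual exclusions used for the pre/post assessment do not carry over to the stepped-wedge part. On data sources, the Outcomes section says: "CCC data will be retrieved from facility electronic medical records and patient files, focusing on routinely collected HIV care indicators".

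Stigma appears as a measured variable in one place, under Quantitative Data Collection and Storage: "The survey includes validated and pilot-tested modules on sociodemographics, technology acceptance, HIV-related stigma". That survey takes about 40 minutes and is given after individual written consent. Participants and Recruitment limits it to men who own a smartphone or tablet, started care in 2016 or later and have no severe comorbidity. They are recruited at routine clinic visits, with a target of 347. Results reports 307 recruited.

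**The concern.** The covariate list belongs to one component of the study and the data to fill it belong to the other. A model containing stigma can use only men with a stigma score. On the data flow described, roughly five in six of the men in the stepped-wedge population have none. Gender shows that the list was not checked against the population, although a constant term simply drops out and does no numerical harm.

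Two things are at stake. One is power: the stated figure needs all 1899 men. The other is who is analysed. Men with survey data are selected on device ownership, treatment start date, comorbidity, consent and presence at a clinic visit. The primary outcome is missed appointments, so recruiting at visits selects on behaviour close to that outcome. This sits badly with an intention-to-treat analysis of all men in care at each facility.

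**Working it through.** **Inputs.** Facility sizes are 758, 294, 598 and 249 (Study Setting). The power section gives the baseline and number of periods ("assuming baseline missed-appointment proportion (p0) of 20% (0.20) and 5 periods"), the odds ratio 0.75, the intracluster correlation 0.02 and power of about 80%. The two-sided 5% level is in Stepped-Wedge Analysis. Survey counts are 347 (Participants and Recruitment) and 307 (Results).

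**Assumptions.** One facility crosses at each step. Every man contributes one binary outcome in every period. The survey subset is spread over facilities in proportion to their size. Rollout order depends on readiness and is not stated, so all 24 orders were run.

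**Share of men with survey covariates.**
- 307/1899 = 16.2%, leaving 1899 − 307 = 1592 men without a stigma score.
- 347/1899 = 18.3%, leaving 1899 − 347 = 1552.

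**Effect on the proportion scale.**
- Baseline odds are 0.20/0.80 = 0.25. Under the intervention, odds are 0.25 × 0.75 = 0.1875.
- p1 = 0.1875/1.1875 = 0.158, so the difference is d = 0.200 − 0.158 = 0.042.
- Mean proportion is 0.179, so σ² = 0.179 × 0.821 = 0.147.
- Between-facility variance is τ² = (0.02/0.98) × 0.147 = 0.0030.

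**Hussey-Hughes variance.** For facility i with n_i men per period, the five period means have covariance V_i = (σ²/n_i)·I + τ²·J, where J is the matrix of ones. With D_i holding the period indicators and the exposure column, SE² is the exposure entry of (Σ D_i′V_i⁻¹D_i)⁻¹. Power is Φ(d/SE − 1.96), plus a negligible opposite tail.

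| Men per period | SE over the 24 orders | Power |
|---|---|---|
| 1899 | 0.0143–0.0152 | 79.0–83.6% |
| 347 | 0.0326–0.0347 | 22.9–25.2% |
| 307 | 0.0346–0.0367 | 20.9–23.0% |

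The first row reproduces the plan's figure of about 80%. As a hand check of its lower end: 0.0421/0.0152 = 2.77, and Φ(2.77 − 1.96) = 0.79. The loss is close to what sample size alone implies, since √(1899/307) = 2.5.

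**Robustness.** The same calculation on the logit scale gives 79.9–84.4% at 1899 men, 24.0–26.6% at 347 and 21.9–24.3% at 307. A logistic simulation with 1500 replicates and random rollout order gave 81%, 23% and 21%. At an odds ratio of 0.70 with 307 men, power is about 31–32% (simulation 30%).

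**The case against.** The strongest reply is that the article never says the adjusted model is the primary one. The core model is defined first, the covariates come in a separate sentence, and the power calculation mentions no covariates. If the unadjusted model carries primary inference, the loss falls only on an adjusted analysis. This stands. A reader might infer that the primary analysis, run as written, necessarily shrinks to 307 men, but the text does not support so firm a claim.

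The collapse also assumes complete-case fitting. That is the default of the Stata commands named, not a stated rule, and handling of missing covariates is often left to an analysis plan that is not shown. This stands as a limit on the size of the effect. It does not rescue the list: imputing stigma for more than 80% of men would lean almost wholly on the imputation model, and nothing can make gender vary.

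That income and education come only from the survey is an inference from its sociodemographic module; patient files might hold them. This stands too, but stigma alone causes the loss. The list also serves several outcomes, and for any outcome collected in the survey the survey covariates would be usable. The primary outcome comes from records.

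A reader might go further and fault facility size and urban/rural, because "Mbita and Ndhiwa subcounty hospitals are situated in an urban setup" and these are also the two largest sites. That is not upheld. No effect of these covariates on bias or power has been shown. The planned random intercepts do not by themselves remove such covariates, and the Limitations section already discloses the restricted facility-level adjustment.

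**Conclusion.** The concern holds in a conditional form. The prespecified patient-level list cannot be applied to the 1899-man population from the data sources the article describes. Stigma is documented only in the survey, income and education probably so, and gender is constant. This is a conflict between stated elements, not a detail left to a later document.

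The consequence depends on two points the article leaves open: whether the adjusted model is primary, and whether it is fitted to complete cases. If both are so, the analysis keeps 16 to 18% of the men and power at an odds ratio of 0.75 falls from about 79–84% to about 21–25%, in a subset selected partly on clinic attendance. If the unadjusted model is primary, the powered analysis survives and only the adjusted one is affected.

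The range 307 to 347 is used because Results reports 307 recruited but also says baseline collection had finished in only three facilities.

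**What to change.** In Stepped-Wedge Analysis, state that primary inference for missed appointments comes from the model with period, exposure and facility effects, adjusted only for covariates held in the records of all 1899 men (age, for example). Delete gender. Move stigma to a secondary analysis in the survey subset and to the adoption analyses, labelled as such with its reduced sample. Do the same with income and education unless the records hold them for every man; if they do, say so. This still allows the interpretation by education and stigma foreseen in the Discussion.

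The cost is a change of wording, with no new data collection. The downside is that the primary estimate is not adjusted for survey-only variables. Follow-up is expected to finish in August 2026 with analysis after it, so the change can be made before outcomes are analysed.

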**Methods:**

We will use a mixed methods design combining a stepped-wedge cluster approach and a pre- and postimplementation assessment across 4 health facilities in Homa Bay County, Kenya. Approximately 347 men receiving HIV treatment who own a smartphone will be enrolled. The stepped-wedge design will sequentially introduce the intervention across the 4 facilities in 2-month intervals following baseline assessments, allowing each site to serve as its own control. Surveys will collect data on sociodemographics, masculinity, intervention acceptability and uptake, and HIV clinical outcomes using validated measures. Intervention effects on pre- and postbinary outcomes will be assessed using the McNemar test, while generalized estimating equations (*α*=.05; *β*=.2; 95% CI) will account for clustering and repeated measures in the stepped-wedge analysis. Focus group discussions (n=5-6) will be conducted with men living with HIV, health care providers, and app developers to explore barriers and facilitators of implementation and adoption. Focus group discussions will be audio-recorded, transcribed, coded, and analyzed thematically.

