## Methods

### Study Design

This study will use an explanatory sequential mixed methods design, combining quantitative and qualitative approaches to understand both implementation outcomes and contextual factors influencing intervention uptake [32]. The quantitative component will use a stepped-wedge approach across 4 health facilities (n=1899) [33,34] analyzed using generalized linear mixed models to account for clustering and repeated measures [34,35] with pre- and postassessment of implementation outcomes [36,37] (n=347; Figure 1). The qualitative component will involve thematic analysis of focus group discussions (FGDs; 5‐6 groups of ~6 key stakeholders) across 4 health facilities in Homa Bay County (Table 1). This analysis will combine deductive coding guided by Proctor’s implementation outcomes framework with inductive coding to capture emergent themes [36]. This integrated approach ensures rigorous evaluation of the Nishauri mHealth intervention across multiple levels and stakeholder perspectives.

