### Stepped-Wedge Intervention Approach

#### Strategy

A stepped-wedge design was chosen to allow all facilities to receive the intervention, accommodate phased training and app deployment, minimize contamination between sites, and enable within-facility comparisons over time while controlling for secular trends. The 4 CCCs will undergo a standardized readiness assessment, and phased implementation of the intervention will proceed in sequence according to facility readiness, with sites transitioning from standard care to the mHealth intervention arm over an 8-month period. The phased rollout will occur at 2-month intervals across the 4 participating facilities, resulting in 5 study periods (1 baseline and 4 intervention steps) over approximately 8 months. The 2-month interval was selected to align with routine HIV clinic visit schedules in Kenya [18], allow sufficient time for provider training and participant onboarding, and permit stabilization of app engagement before subsequent facility transitions. This interval is consistent with stepped-wedge evaluations of health service and digital interventions [42] and supports the detection of short-term changes in missed clinic visits and adherence behaviors while accounting for secular trends.

We acknowledge that the 2-month step length is relatively short and may limit detection of longer-term intervention effects within each wedge; however, this interval was selected for programmatic feasibility and alignment with routine HIV care cycles, and outcome measures were therefore chosen to capture proximal, short-term indicators of engagement and retention.

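### Cluster-robust standard errors on four facilities do not secure valid inference: the planned test rejects a true null about 22-29% of the time at a nominal 5%

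*Protocol article*

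**What the plan says.** The Stepped-Wedge Analysis section specifies a generalized linear mixed model with fixed period effects, a fixed exposure indicator and "random intercepts for clusters (facilities) to account for within-cluster correlation". Random slopes for time may be added if the data support them. It then says "We will use robust SEs (cluster-robust SEs) to ensure valid inference with a limited number of clusters" and sets primary inference as two-sided at 0.05. It mentions no small-sample correction, t reference or adjusted degrees of freedom.

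On the model class, the Study Design section has the trial "analyzed using generalized linear mixed models to account for clustering and repeated measures", whereas the abstract gives the task to generalized estimating equations, which "will account for clustering and repeated measures in the stepped-wedge analysis".

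On the design, the Strategy section says "The phased rollout will occur at 2-month intervals across the 4 participating facilities", "resulting in 5 study periods (1 baseline and 4 intervention steps" over about 8 months. It adds that "phased implementation of the intervention will proceed in sequence according to facility readiness". The power section gives the sizes: "With facility totals of 1899—Mbita (n=758), Ogongo (n=294), Ndhiwa (n=598), and Pala (n=249".

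The Limitations section concedes that few clusters may limit power, restrict control of facility-level confounding and reduce degrees of freedom for random effects. It does not withdraw or qualify the statement about robust standard errors.

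**The concern.** A cluster-robust variance estimates the variability of the intervention effect from the spread of the cluster-level score contributions. Here there are four. With so few, the estimate is biased low and very unstable, and a Wald statistic built on it has much heavier tails than the normal. Robust standard errors protect against a misspecified correlation structure when clusters are many. They are not a remedy for having few, which is the purpose the sentence gives them.

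Missed appointments is the primary clinical outcome of the stepped-wedge component. If the test is several times too liberal and the interval correspondingly too narrow, a significant result cannot bear the weight the conclusions intend to put on it.

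**Working it through.** **Inputs from the protocol.** Facility sizes 758, 294, 598 and 249 (total 1899); 5 periods; one facility crossing over per step; baseline missed-appointment proportion 0.20; odds ratio 0.75; ICC 0.02, with sensitivity values up to 0.05; two-sided alpha 0.05.

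**Assumptions added.** The article does not give the scale of the ICC, so both were run. On the logit scale, 0.02 = s²/(s² + 3.29) gives s² = 0.067 and a facility SD of 0.259. On the proportion scale the facility logit SD is about 0.357. The main setting has every man contributing in every period; splitting the men over periods was also run. There is no secular trend, and the rollout order is random.

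**Step 1: the protocol's own power figure.** Odds at 20% are 0.25; times 0.75 gives 0.1875, and 0.1875/1.1875 = 0.158. The Hussey-Hughes generalized least squares variance, with the four actual sizes and averaged over the 24 possible orders, gives:
- Logit scale: ln(1/0.75) = 0.288, SE about 0.0998, 0.288/0.0998 = 2.88, and Φ(2.88 − 1.96) = about 82%.
- Proportion scale: 78.0% (75.5-80.4% over the orders).

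The stated ~80% lies between these. With the men split over the 5 periods power is only 24-27%. So the stated figure implies every man in every period, model-based standard errors and a normal reference. It does not describe the robust test that the analysis section plans.

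**Step 2: type I error of the planned test.** Data were simulated with no intervention effect. The table gives rejection rates at nominal 5%. Ranges cover ICC 0.02 and 0.05, all men in every period or split, and with or without facility-by-period variation. The scaled column multiplies the sandwich by G/(G−1) = 4/3.

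| Analysis | Scaled, normal | Unscaled, normal | Scaled, t(3) |
|---|---|---|---|
| Random-intercept GLMM (Methods) | 21.6-24.4% | 27.2-29.3% | 7.5-10.5% |
| GEE, exchangeable (abstract) | 22.1-25.1% | 28.5-30.9% | 8.1-11.7% |
| GEE, independence (abstract) | 27.2-34.5% | 33.0-39.9% | 11.4-16.2% |

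These are 1000 runs per setting. The Monte Carlo SE at 22% is √(0.22 × 0.78/1000) = 1.3 points. Logistic regression with fixed facility effects and the scaled sandwich gave 22.3-24.4% (3000 runs per setting). A further 4000-run check of that model gave 24-25% scaled, 29-31% unscaled and 9-11% with t(3).

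**Step 3: comparison with model-based standard errors.** For the same GLMM, model-based standard errors reject 4-8% when the random-intercept model is correct, so there the robust step creates the error. With facility-by-period variation (cluster autocorrelation about 0.83, all men every period) the model-based test rejects about 16% and the robust test 24-28%. Neither is adequate.

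**Step 4: an analysis that holds its level.** Fit logistic regression to the 20 facility-by-period counts with fixed facility and period effects, and scale the standard error by the Pearson dispersion. Residual degrees of freedom are 20 − 4 − 4 − 1 = 11. The facility logit SD is 0.357.

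| Facility-by-period share of facility variance | Type I error, t(11) | Power at OR 0.75 |
|---|---|---|
| 0% | 4.3-4.6% | about 72% |
| 10% | about 6% | 47-49% |
| 20% | 6.0-6.4% | about 37% |

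**The case against.** The strongest reply is that a small-sample reference may be intended but condensed out of a journal article, and that the Limitations section already concedes the small number of clusters. The first part is fair about what is unstated, but the finding does not rest on an omission. The sentence makes a positive claim, that robust standard errors supply the validity, and a t(3) reference with the scaled sandwich still leaves about 8-11%. The Limitations section's mitigations (fixed time effects, intention to treat, triangulation with qualitative data) do not correct a standard error.

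Three stronger readings are tempting and are not supported:
- A reader might infer a false-positive rate near 40% for the planned model. In the tabulated simulations rates of that size appear only for GEE with independence working correlation and an unscaled sandwich; the GLMM of the Methods sits at 22-29%.
- A reader might infer that the model allows nothing beyond a facility intercept. The section provides conditionally for random slopes over time.
- A reader might take the lack of a term for repeated observations on the same man as part of the error. An article may leave that detail to the full plan, and this point does not need it.

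A permutation test is no easy escape. The rollout follows readiness, so permuting the order has no basis in the design. Even with a random order the smallest attainable p-value over 24 orders is 1/24 = 0.042.

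It also stands that the replacement analysis is one choice among several, that it loses power, and that it cannot carry patient-level covariates.

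**Conclusion.** The point holds. The sentence on robust standard errors is wrong as written. For the planned random-intercept model the real level of a nominal 5% test is about 22-29% with an uncorrected sandwich and a normal reference. The GEE named in the abstract does no better.

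The size rests on the assumptions listed with the inputs, but changing the ICC, its scale, or whether men are split over periods moved the GLMM result by only a few points. The simulations say nothing about bias from sequencing facilities by readiness. That is a separate threat which no choice of standard error addresses.

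**What to change.** 1. Delete the statement that cluster-robust standard errors ensure validity with few clusters.
2. Name one primary analysis, identically in the abstract, Study Design and Stepped-Wedge Analysis, with inference that is valid for four clusters. One that works is logistic regression on facility-by-period counts with fixed facility and period effects, a Pearson-dispersion-scaled standard error and a t reference on 11 degrees of freedom.
3. Say openly that this primary model leaves out the prespecified patient-level covariates, which move to a secondary adjusted model, and that the fixed facility effects absorb facility size and urban or rural setting.
4. Restate the ~80% power for the analysis chosen, with the assumed facility-by-period variation.

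No data collection changes, but the cost is more than wording. Intervals widen, and the trial may fall well short of its stated power, as the last table in the working shows. That loss should be stated, and the readiness-based order should be given as a remaining source of bias.

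### The one named check for a changing effect crosses exposure with calendar step, which has little power for build-up after each facility's own rollout; a tested time-since-rollout analysis should be added

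*Protocol article*

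**What the plan says.** The Strategy section sets out four facilities crossing over at two-month intervals, "resulting in 5 study periods (1 baseline and 4 intervention steps) over approximately 8 months". One facility crosses at each step, in order of readiness, so all four are exposed in the fifth period.

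The Stepped-Wedge Analysis section gives the model. "Models will include a fixed effect for time period (step) to account for secular trends", next to one exposure indicator and "random intercepts for clusters (facilities) to account for within-cluster correlation". Among the sensitivity analyses it lists "models testing for time-by-intervention interaction to explore whether effect sizes change across steps". It names no term for time since a facility's own rollout. The other items listed, random slopes for time and a per-protocol analysis, do not test whether the effect changes with duration of exposure.

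Two places bear on when an effect might appear. Strategy explains the two-month step partly by the need to train, onboard and "permit stabilization of app engagement before subsequent facility transitions". Implementation Outcomes counts a man as an adopter if he installs and activates the app within 60 days of introduction, which is about one step.

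**The concern.** An app that men install over several weeks may affect missed appointments gradually, or its effect may fade. Either pattern runs on each facility's own clock, starting at its rollout. A calendar step mixes facilities at different points on that clock: in period 4 the three exposed facilities are in their first, second and third exposed steps. Averaging over them blurs the pattern that the check should reveal.

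The primary model has a single exposure indicator and so assumes one constant effect. If the effect is delayed, facilities exposed earlier are still improving while they serve as comparators for facilities that have just crossed. This pulls the estimate towards no effect or beyond. The interaction check is the only safeguard the article names against that. If it is nearly blind to the pattern, the trial could report no effect and no sign of a changing effect while a real benefit began one step after rollout.

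**Working it through.** **Inputs.** From Power Estimation for Stepped Wedge Analysis: facility sizes 758, 294, 598 and 249 (total 1899), p0 = 0.20, ICC = 0.02, OR 0.75, 5 periods, two-sided alpha 0.05. Assumptions: all 1899 men contribute in every period, the facility effect is stable over time, and tests are large-sample. The rollout order is not fixed, so all 24 orders were used.

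**Layout.** Steps since rollout (0 = not yet exposed):

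| Facility, by rollout order | P1 | P2 | P3 | P4 | P5 |
|---|---|---|---|---|---|
| First | 0 | 1 | 2 | 3 | 4 |
| Second | 0 | 0 | 1 | 2 | 3 |
| Third | 0 | 0 | 0 | 1 | 2 |
| Fourth | 0 | 0 | 0 | 0 | 1 |

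**Estimability.**
- Five period terms plus four exposure-by-period terms make 9 columns of rank 8. The P5 column of the layout has no zero, so exposure in period 5 equals the period-5 indicator. The categorical interaction test therefore has 2 df, not 3.
- A linear time-by-exposure model has 7 columns and rank 7. It is estimable, but its period-5 value is extrapolated.
- Facility, period and four time-since-rollout terms make 12 columns of rank 12. All four effects are estimable.

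**Method.** Generalised least squares on facility-period logits.
- Between-facility variance: ICC/(1 − ICC) × π²/3 = 0.02/0.98 × 3.290 = 0.067.
- Sampling variance of a cell: 1/[n p(1 − p)]. At p = 0.20 this is 1/(758 × 0.16) = 0.0082 for the largest facility and 1/(249 × 0.16) = 0.0251 for the smallest.
- Power comes from the non-central chi-square distribution. The check was 3,000 simulated trials per scenario with binomial counts and likelihood-ratio tests.

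**The plan's own figure.** For a constant OR of 0.75 the protocol states about 80% power. The method gives 81% (79–84% by order) and simulation gives 79.9%, so the figure reproduces. Spreading 1899 men over the five periods would give only 25–27%, so the stated power needs the full cohort in each period. Under a constant effect, every interaction test rejected in about 5% of simulated trials, as it should.

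**Power to detect a changing effect.** Patterns are shares of log(0.75) at steps 1, 2, 3 and 4 since rollout. Row 1 is the average over orders with its range, rows 2–4 are simulated, and row 5 is the average over orders, with ranges across calculation variants.

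| Assumed pattern | Calendar, categorical | Calendar, linear | Since rollout, joint 3 df | Since rollout, linear | First vs later, 1 df |
|---|---|---|---|---|---|
| 0, 1, 1, 1 | 16% (9–25) | 18% (10–28) | 67% (64–71) | 58% (49–68) | 82% (79–85) |
| ½, 1, 1, 1 | 8.0% | 8.3% | 20.0% | 19.4% | 29.5% |
| ¼, ½, ¾, 1 | 6.5% | 6.9% | 14.5% | 21.8% | 13.7% |
| 0, ⅓, ⅔, 1 | 8.0% | 9.4% | 23.6% | 34.8% | 21.7% |
| 0, 0, 1, 1 | 10% | 11% | 50–52% | 43–45% | 10% |

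Simulation for the first row gave 15.7%, 17.8%, 66%, 56% and 80.8%. For waning (1, 1, ½, 0), first-versus-later has about 7%, against 7–8% for the calendar test, so that contrast gains nothing.

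**Effect on the primary estimate.** Under the first pattern the constant-effect model estimates an OR of about 1.00 (0.98–1.02 by order), with 5–6% power.

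**Facility-by-period drift.** With an assumed cluster autocorrelation of 0.8, the first row falls to 8–9% for the calendar tests, against 26–42% for the time-since-rollout tests. Another way of building in the drift gives about 56% for first-versus-later. Four clusters with robust standard errors add uncertainty that these large-sample figures do not carry.

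**The case against.** The strongest reply is that this is an exploratory sensitivity analysis in a condensed article. Primary inference rests elsewhere, and a fuller plan may code the interaction differently or add exposure-time terms. Strategy already concedes that short steps may limit detection of longer-term effects, and Limitations concedes low power with few clusters. A calendar-step interaction also answers a legitimate question of its own. All of this stands. It limits the weight of the point and argues for adding an analysis rather than replacing one. It does not remove the point, because the article has chosen a check and an axis, and a plan that follows it would inherit both.

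Three stronger readings might be inferred, and the documents support none of them.

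- **That the contrast is generally 16–18% against about 80%.** The 80% requires no effect in the first exposed step, full effect afterwards, and a contrast cut exactly there. For a two-step delay or waning, that contrast does no better than the calendar test.
- **That the interaction cannot be estimated.** Only a period-5-specific effect with categorical steps is unidentified. The joint test over the identifiable steps does not depend on which aliased column the software drops, and the article does not say whether time is categorical or linear.
- **That the plan predicts a null first step.** Strategy speaks of engagement settling before the next facility crosses, that is, within the step, and says the interval suits short-term changes. The 60 days define adoption and are not a stated lag. A partial first-step effect fits the text at least as well, and there the gain is from about 8% to at most about 30%.

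Nor does the article say that a non-significant interaction will be taken as proof of a constant effect. That is a risk to guard against, not a stated intention.

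**Conclusion.** The point holds as a weakness in the chosen sensitivity analysis. On the natural reading, the one named check uses calendar step. Its period-5 effect is unidentified if steps are categorical and extrapolated if time is linear. It has low power, 7–18% on average, for every delayed pattern tried.

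A time-since-rollout analysis does better for all of these patterns when it is general (joint or linear). The improvement ranges from large (one-step delay: 16–18% to 67%) to modest (gradual ramp: about 7% to 14–22%). Under a full one-step delay the primary estimate would be near 1.0, so the safeguard matters.

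The figures assume the full cohort in each period, p0 0.20, ICC 0.02, no facility-by-period drift and large-sample tests. The delay shapes are assumptions, not figures from the documents. Neither the sample size nor trial conduct is affected.

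**What to change.** In Stepped-Wedge Analysis, add a sensitivity analysis that replaces the single exposure indicator with effects at 1, 2, 3 and 4 steps since rollout, reports all four with confidence intervals, and tests their equality jointly on 3 df. Name first exposed step versus later steps as a supplementary 1-df contrast, not as the main test.

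If the calendar-step interaction is kept, restrict it to periods 2–4 and state that a period-5-specific effect is not identified. For either analysis, state that a non-significant result will not be read as evidence of a constant effect.

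The cost is a sentence or two and one extra model, with the same data and software. Results indicates that follow-up runs to August 2026, so the change can be made before analysis. The drawback is that the added test still has modest power for gradual changes, so the four estimates and their intervals should carry the interpretation.
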